### Assessment of costs

Cost evaluation will be conducted to record the additional costs of implementing the self-acupressure training course for knee OA in the community centre setting from the perspectives of health service providers. Total costs will be summation of interventional costs, direct medical costs and direct non-medical costs.

Interventional costs will be included such as staff costs for organizing the course and running the course, telephone follow-up after the course, teaching materials, consumable materials, and rental cost of venue. To estimate the time cost of staff for organizing and preparing the course, the time spent on the program by each staff member (instructor, course assistant, and research assistant) will be recorded for

each course. The average number of minutes spent will be multiplied by the relevant salary rate per minute. The cost of teaching materials including the handouts, and other consumable will also be calculated. Besides, direct medical costs will account for the number of healthcare service visits during the trial period, whereas the direct non-medical costs will estimate transportation costs related to intervention and course attendance.

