### *Economic analyses*

Quality-adjusted life-years (QALYs) will be obtained from the SF-6D (22). Cost evaluation will be conducted to record the costs of implementation in the community setting from the perspectives of health service providers. Incremental costs and incremental effects will be compared between the self-acupressure and KHE groups. The incremental cost-effectiveness ratio (ICER) will be calculated by:  $\Delta \text{ costs} / \Delta \text{ effects}$ , where  $\Delta \text{ costs}$  represents the difference in the costs between self-acupressure and KHE groups, and  $\Delta \text{ effects}$  represents the difference in the QALYs (changes in SF-6D scores) between the two groups.

To test the robustness of the ICER and quantify the uncertainty in these ratios, bootstrapping involving 5,000 iterations will be performed and the results will be

plotted in a cost-effectiveness plane. A cost-effectiveness acceptability curve displaying the probability that the intervention is cost effective for a range of willingness-to-pay ceilings will also be estimated by using the bootstrapped ICERs in probabilistic sensitivity analysis. To confirm the robustness of the base-case findings, scenario analysis will be conducted by testing several assumptions made in the base-case scenario. Impacts of these assumptions on the ICER will be assessed.

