## **6. Purpose and Potential**

The findings of this project will be critical in determining the clinical effectiveness of offering a short acupressure training course to teach middle-aged and older to perform self-administered acupressure to relieve their knee pain. Knee OA is a prevalent condition leading to many negative health consequences, and it is expected to be more prevalent due to the aging population.

Self-administered acupressure is less time-consuming and at minimal cost. If found to be effective, we can recommend self-administered acupressure as an evidence-based strategy to healthcare providers for relieving knee OA pain in the community. Effective self-administered acupressure treatments could be made available to people knee OA in the community as an adjunct intervention to their current pain therapy and probably reducing their consumption of painkillers and prevent deterioration of their condition. The self-administered acupressure can be taught by Chinese medicine practitioners and other healthcare professionals such as nurses or physiotherapists. This cost-effective method will significantly relieve the burden on the public healthcare system. Healthcare providers, public health policy-makers, and individuals with knee OA will greatly benefit from the findings of this study.

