| Fast Gait Speed                                                 |           | √        |                              |   | √                         | √ | √  |
| Medication Use                                                  |           | √        |                              |   | √                         | √ | √  |
| Others                                                   |           |          |                              |   |                           |   |    |
| Acupressure/ health instruction logbook                         |           |          | √                            | √ | √                         | √ | √  |
| Adverse event monitoring                                        |           |          | √                            | √ | √                         | √ | √  |

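### The ICER's direct medical costs rest on healthcare visits with no stated source or timing, and analgesic use, already recorded in both arms, is not listed as a cost

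*Protocol*

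**What the plan says.** Protocol section 4, Assessment of costs, builds the total from three parts: "Total costs will be summation of interventional costs, direct medical costs and direct non-medical costs". The only content given for the second part is that "direct medical costs will account for the number of healthcare service visits during the trial period". The third part is transport related to the intervention and to attending the course. For the first part a source is given for staff time: "the time spent on the program by each staff member (instructor, course assistant, and research assistant) will be recorded for" each course.

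Section 5, Economic analyses, forms the ICER from a between-arm cost difference, which "represents the difference in the costs between self-acupressure and KHE groups". It then plans 5,000 bootstrap iterations, a cost-effectiveness plane, an acceptability curve and scenario analyses. The stated viewpoint is that of the provider: "Cost evaluation will be conducted to record the costs of implementation in the community setting from the perspectives of health service providers".

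Medication Use is a secondary outcome. Analgesics are written in a logbook throughout the study, and Table 1 ticks Medication Use at baseline and weeks 4, 8 and 12. Section 6 expects acupressure to be "probably reducing their consumption of painkillers".

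**The concern.** A cost component that enters the ICER needs a data source that works the same way in both arms. For healthcare visits the protocol names none. If visits are not asked about during the trial, they can be recovered later only from records that the protocol does not mention, or by long recall from participants who opened their own allocation envelope and so know their group.

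Drug costs have the opposite problem: the data will exist but are not costed. Section 6 points to lower painkiller use and less burden on public healthcare as benefits. An ICER that omits the first, and has no stated way of counting the visits that bear on the second, says little about either.

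**Working it through.** No figure in the protocol can be recomputed here: it gives no unit costs, visit rates or drug costs. The check sets the cost definition beside every place where data collection is described.

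**Where could a visit be recorded?**

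- Acupressure logbook (Treatment protocol; Monitoring of compliance, intervention group; Assessment of compliance): frequency, time and duration of practice. No visits.
- Control logbook (Monitoring of compliance, control group; Assessment of compliance): yes/no adherence to each instruction. No visits.
- Control logbook as described under Knee health education control group: daily pain management. A visit might be noted there, but visits are not named and no counterpart is described for the acupressure arm.
- Medication Use (section 4): usual physician visits may continue, but only analgesics are to be written down.
- Assessment of safety: withdrawal reasons and adverse events only.
- Table 1: rows for vital signs, the outcome measures, Medication Use, "Acupressure/ health instruction logbook" and adverse events. No row for healthcare use.

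Result: visits are in the cost definition, but no source or time point is named in either arm. Staff time, in the same section, does have a stated source.

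**Where are analgesics costed?** They are recorded for all participants, but appear neither in Assessment of costs nor in Economic analyses.

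**What does the omission do to the ICER?** Write the cost difference (acupressure minus KHE) as

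ΔC = ΔC(intervention) + ΔC(visits) + ΔC(transport),

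and let ΔD be the difference in analgesic cost. Then

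- ICER as written = ΔC / ΔQALY
- ICER with drugs = (ΔC + ΔD) / ΔQALY
- as written minus with drugs = −ΔD / ΔQALY

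If the protocol's own expectation holds (ΔD < 0) and ΔQALY > 0, the ICER as written is too high, so the omission counts against acupressure. If ΔD > 0 the sign reverses. Without unit costs neither ΔD nor the visit term can be given a value.

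**Does equal contact time settle the rest?** Scheduled minutes, from the session descriptions:

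- Acupressure session 1: 20 + 30 + 30 + 30 + 10 = 120
- Acupressure session 2: 20 + 30 + 30 + 30 + 10 = 120
- KHE session 1: 30 + 30 + 30 + 15 + 15 = 120
- KHE session 2: 15 + 30 + 30 + 30 + 15 = 120

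The minutes are equal, but cost is minutes multiplied by a salary rate. A registered Chinese medicine practitioner with a Master's degree and at least 5 years' experience teaches one arm, and a registered nurse the other. The acupressure arm also has a video, possible additional training and a technique check at week 4. Equal minutes therefore do not show that ΔC(intervention) is near zero.

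**The case against.** The strongest reply is that visits are in the plan and only the form is unnamed. Case report forms are not at hand. Table 1 is not a complete list either: it also leaves out training attendance, the evaluation questionnaire, the week 4 technique check and staff time, all of which the text promises. This stands, and it limits the point to a source that is not stated. A reader might infer that no participant-level medical cost can exist; the protocol does not support that, since it commits the trial to accounting for visits.

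A second reply is that drugs bought by participants fall outside a provider perspective, so leaving them out may be deliberate. This stands in part. The protocol does not say so, however, and it already counts transport for attending the course, presumably participants' own travel, which a strict provider perspective would also exclude. As written, the perspective does not clearly put analgesics in or out.

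A reader might also infer from the equal session times that nearly all of the cost difference lies in visits and drugs. The differing instructors and the extra acupressure components rule out that conclusion.

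Nor should one conclude that KHE course costs will go uncollected. The aim to "record the additional costs of implementing the self-acupressure training course for knee OA" mentions one course only, but the ICER definition requires both arms' costs. This is a wording matter.

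**Conclusion.** The point holds in a limited form. Direct medical costs depend on visit counts for which the protocol names no source or time point in either arm. Analgesic use is recorded in both arms but is in no cost definition, although the protocol expects it to change. The planned ICER and its bootstrap would therefore omit drug costs and rest partly on visit counts whose quality and comparability between arms are unknown.

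The size cannot be stated. The direction of the drug omission follows only if one assumes that analgesic use falls more with acupressure and that QALYs rise. The conclusion also assumes that no form outside the protocol already asks about visits in the same way in both arms; if one does, citing it settles that half.

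Unit costs and costing detail may properly sit in an analysis plan that is not shown. Visit data that were never collected cannot be supplied by one. Severity is minor: the primary outcome, the hypothesis and both specific aims do not depend on the economic analysis.

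**What to change.** 1. Add a healthcare-visit question to the assessments at weeks 4, 8 and 12, on one form used identically in both arms, with recall back to the previous assessment, and add the matching row to Table 1. Participants still know their group, but each recall period is about 4 weeks (12 / 3) instead of up to 12.
2. Include analgesic cost, from the Medication Use data already collected, in direct medical costs, either in the base case or as a named scenario among those already planned. State how this and the transport costs fit the provider perspective.
3. As a wording clarification, say that staff time, materials and venue are recorded for KHE classes in the same way as for acupressure classes.

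Cost: a few extra questions at visits already scheduled and a unit-cost lookup for analgesics. No added visit is needed.

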## **5. Data processing and analysis**

### *Sample size calculation*

Results from our pilot study (N=35) of self-administered acupressure for knee OA are used for sample size calculations. At week 6, the mean (SD) of NRS in the self-administered acupressure group and knee health education group was 2.83 (1.47) and 2.07(1.58), respectively. It equals to an effect size of 0.49. With a more conservative approach, we use 80% of the effect size, which is 0.40 for the sample size calculation. A sample size of 133 subjects per group can provide 90% power to reject the null hypothesis with a significance level of 0.05. Assuming an attrition rate of 15%, a total of 314 subjects is required for this study.

### *Data management and analysis*

All data will be double entered. All statistical analysis will be performed in SPSS (23.0) for Windows. Subjects' sociodemographic, clinical characteristics and baseline data was examined for potential group difference and any identified baseline difference was controlled as covariates. The changes of the primary outcome (NRS score) and other secondary outcomes were compared using linear mixed effects model with group (self-administered acupressure and knee health education) by time point interaction (baseline to week 12). Acceptability and compliance will be presented using descriptive statistics. Clinical significance will be examined by the proportion of participants who have a reduction of at least 2 points from baseline in the NRS using Chi-square test (25). The intention-to-treat analysis will be conducted.

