## Supplement 1. Study Protocol

# Title: Self-administered Acupressure for Knee Osteoarthritis in Middle- and Older-Aged Adults: A Randomized Controlled Trial

## Abstract

**Objectives:** To evaluate the short- and medium-term effectiveness of self-administered acupressure taught by a short training course on reducing knee osteoarthritis (OA) pain in middle-aged and older adults.

**Hypothesis:** The self-administered acupressure group would have a greater pain relief compared to the knee health education (KHE) control in subjects with knee OA at week 12 (medium-term).

**Design and subjects:** In this fully-powered randomized controlled trial, 314 participants with knee OA recruited from the community will be randomized to self-administered acupressure or KHE group in a 1: 1 ratio.

**Study instrument:** Numerical rating scale (NRS) will be used to assess pain intensity in the knee.

**Interventions:** Participants in the self-administered acupressure will attend two 2-hour training sessions (1 week apart) to learn self-administered acupressure and practice twice daily for 12 weeks. Participants in the control group will receive knee health education of the same schedule and duration.

**Main outcome measures:** The primary outcome measure is the NRS score at 12 weeks. Other outcomes include Western Ontario and McMaster University Osteoarthritis Index, Short Form Six Dimensions, Timed Up & Go Test, Fast Gait Speed, pain medication usage. Compliance of self-administered acupressure will also be evaluated.

**Data Analysis:** Differences in the scale scores and test parameters will be examined using a linear mixed-effects model.

**Expected results:** Subjects in the self-administered acupressure group will have greater improvement in NRS and other related parameters compared to those in the KHE group at week 12.

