## 2. Aims and Hypotheses:

We hypothesize that the self-administered acupressure group would have a greater pain relief compared to the knee health education control in subjects with knee OA at week 12 (medium-term).

The specific aims are:

1. To examine the short- and medium-term effectiveness of self-administered acupressure taught by a short training course on relieving knee OA pain in middle-aged and older adults.
2. To evaluate the subjects' compliance with self-administered acupressure for knee OA.

To achieve these aims, we will perform an RCT on self-administered acupressure for alleviating knee OA pain delivered through a short training course using a knee health education course as a control.

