### Methods

The proposed study is a **randomized controlled trial (Figure 1)**. Participants will be randomly assigned to receive 2 training sessions (2 hours each) of either

**self-administered acupressure or knee health education** in 1:1 ratio. Participants in the self-administered acupressure group will be told to perform the self-administered acupressure twice a day for 12 weeks, and participants in the knee health education group will follow the knee health instruction every day for 12 weeks. Reminders for practice will be sent to the participants via WhatsApp. Outcome measures will be assessed at baseline, week 4, 8, and 12. Ethical approval from the institute will be sought before commencement of the study. We will follow the CONSORT and STRICTA for the report of the trial and acupressure protocol.

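### The primary comparison is a group-by-time interaction over baseline to week 12 and is not tied to the declared primary outcome, NRS at week 12

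*Protocol*

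**What the plan says.** The Abstract states: "The primary outcome measure is the NRS score at 12 weeks". The hypothesis in section 2 is likewise about pain relief "compared to the knee health education control in subjects with knee OA at week 12 (medium-term".

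The Methods section sets four visits: "Outcome measures will be assessed at baseline, week 4, 8, and 12".

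Section 5, Sample size calculation, treats the trial as one comparison of two group means. It takes the pilot effect and says "we use 80% of the effect size, which is 0.40 for the sample size calculation", then "A sample size of 133 subjects per group can provide 90% power to reject the null hypothesis" "with a significance level of 0.05". It gives no correlation between visits and no course of the effect over time.

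Section 5, Data management and analysis, then says "The changes of the primary outcome (NRS score) and other secondary outcomes were compared using" a "linear mixed effects model with group (self-administered acupressure and knee health education) by time point interaction (baseline to week 12". The same sentence serves the primary outcome and the secondary outcomes. It names neither a joint test over all visits nor a contrast at week 12. Covariates enter only where a baseline difference between the groups has been found.

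**The concern.** The outcome, the hypothesis and the sample size all concern a single group difference. The analysis names a model term that, with four visits, can yield more than one test.

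With visit as a categorical factor, the test usually reported for a group-by-time interaction has 3 df. It asks whether the arms differ in change from baseline at any of weeks 4, 8 or 12, in any direction. A significant result could therefore come from an early benefit that has gone by week 12. Such a course is not far-fetched here, since both training sessions and the telephone follow-up fall in the first two weeks. Conversely, an effect that builds slowly to week 12 is spread over three df, and the sample size calculation did not allow for that.

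The other reading is the group difference in change between baseline and week 12, a 1-df contrast that does address the hypothesis. The two readings test different hypotheses with different power. Unless the choice is written down, it can be made after the results are known.

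**Working it through.** **The plan's own figure.** Inputs from section 5: d = 0.40, alpha 0.05 (taken as two-sided), power 90%, attrition 15%.

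- n = 2(1.960 + 1.282)² / 0.40² = 131.4, so 132 per arm. The t-test version gives 132.3, so 133.
- 133 / 0.85 = 156.5, so 157 per arm and 314 in total.

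The stated 133 and 314 reproduce. The 90% is therefore the power of one two-group comparison of means.

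**Assumptions not in the documents.** Complete data on 133 per arm, equal SD at each visit, and compound symmetry with between-visit correlation ρ of 0.3, 0.5 or 0.7. Effects are in score SDs unless stated otherwise.

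**Reading A: joint 3-df interaction.** The group differences in change at weeks 4, 8 and 12 have covariance (2/n)(1−ρ)(I + J), where I is the identity matrix and J the matrix of ones. The inverse of I + J is I − J/4, so the noncentrality is

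λ = (133/2) × [Σδ² − (Σδ)²/4] / (1−ρ),

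and power comes from the noncentral chi-square with 3 df (critical value 7.81).

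- Fading effect 0.4, 0.2, 0: bracket = 0.20 − 0.36/4 = 0.11, so λ = 7.315/(1−ρ) = 10.45 at ρ = 0.3 and 14.63 at ρ = 0.5. Rejection rate **78% and 91%**, with no week-12 effect at all.
- Linear rise to 0.40 (0.133, 0.267, 0.40): bracket = 0.2489 − 0.64/4 = 0.0889, so λ = 5.911/(1−ρ) = 8.44, 11.82 and 19.70. Power **68%, 83% and 97%** at ρ = 0.3, 0.5 and 0.7.
- Constant 0.40 from week 4: bracket = 0.48 − 1.44/4 = 0.12, so λ = 7.98/(1−ρ). At ρ = 0.5, λ = 15.96 and power is 93%.

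An F test with 3 and 264 df lowers these figures by at most one percentage point. The price of the extra df alone can be seen by giving the 3-df test the planned single contrast's noncentrality, 133 × 0.40²/2 = 10.64: power is then 79%.

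**Reading B: 1-df change from baseline to week 12.** In score SDs, the SD of a change is √(2(1−ρ)), so the effect is 0.40/√(2(1−ρ)). If d = 0.40 is already in change-score SDs, the planned calculation applies directly and power is 90%.

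**Baseline-adjusted 1-df week-12 difference.** The residual SD is √(1−ρ²), so the effect is 0.40/√(1−ρ²).

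| ρ | B: standardised effect | B: power | Adjusted: standardised effect | Adjusted: power |
|---|---|---|---|---|
| 0.3 | 0.338 | 78% | 0.419 | 93% |
| 0.5 | 0.400 | 90% | 0.462 | 96% |
| 0.7 | 0.516 | 99% | 0.560 | 99.5% |

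**Other covariance.** Under AR(1) with adjacent-visit correlation 0.3 to 0.8, power is 48% to 79% for the joint test with a linear rise, 72% to over 99% for the joint test with a constant effect, 65% to 91% for the change contrast, and 90% to 97% for the adjusted contrast.

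**Scale of d.** Section 5 labels the pilot values 2.83 (1.47) for acupressure and 2.07 (1.58) for education as NRS means. The higher value would then be the worse one. Read as reductions, they would favour acupressure, but the Introduction gives that group's reduction as 2.27 (SD 1.2). The protocol does not settle whether d is in score or change-score SDs.

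**The case against.** The strongest reply is that the protocol never announces a joint test. It speaks of changes, and of baseline to week 12. Beside an outcome and a hypothesis both fixed at week 12, this can fairly mean the group difference in change at week 12. Under randomisation that contrast estimates the week-12 group difference. This stands. A reader might infer that the planned analysis is not a test of the declared outcome, but that is true only of the joint reading, which the text permits and does not state.

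A reader might also infer that the trial falls short of its 90% power. The documents do not support that either. The change contrast reaches 90% at ρ = 0.5 and 99% at ρ = 0.7, and keeps 90% at any correlation if d is in change-score SDs. Even the joint test reaches 93% with a constant effect at ρ = 0.5. The protocol gives no correlation, covariance structure or trajectory, and the fading-effect scenario is an illustration.

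Finally, the choice of model contrast is often left to a SAP, and none is shown here. That would dispose of a complaint about mere silence. But the protocol does name its comparison, in a form that does not single out week 12, and it makes adjustment conditional on finding a baseline difference. Adjusting for baseline NRS in every case is a better method than the one stated.

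**Conclusion.** The point holds as one of wording and efficiency. The protocol does not say which test from the interaction model decides the trial, and its 90% power is established only for a two-group comparison at one time point. Under the joint reading, the risk is a positive result with no week-12 benefit: 78% or 91% rejection at ρ = 0.3 or 0.5 under the assumed fading effect. Under the change reading, the right question is asked, and whether 90% is reached depends on the correlation and on the scale of d. The power figures rest on the assumed correlations, covariance structures, trajectories and complete data set out above. The ambiguity itself follows from the text alone.

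The baseline-adjusted week-12 contrast met the stated 90% in every case computed with d in score SDs. This is best regarded as a free improvement. It does not show that the trial is underpowered or analysed for the wrong outcome.

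**What to change.** In section 5, Data management and analysis, add wording such as: The primary test is the 1-df between-group difference in mean NRS at week 12, reported with its 95% CI, from the linear mixed model with visit as a categorical factor and baseline NRS adjusted for (or baseline means constrained equal), whether or not a baseline difference is found. Results at weeks 4 and 8 and the overall group-by-time interaction are supportive.

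In Sample size calculation, say whether d = 0.40 is in score or change-score SDs.

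The cost is wording only: same model, same data, same visits, same 314 participants. The text should be fixed before allocation is unblinded for analysis.

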### 3. Subjects

This RCT will recruit 314 participants from the community through advertisement in community centres, radio Health Programme, and newspapers as well as mass email at the University of Hong Kong and the Hong Kong Polytechnic University. Interested participants who provide written informed consent will be further examined for inclusion and exclusion criteria by a trained research assistant.

Inclusion criteria: 1. ethnic Chinese; 2. aged 50 years or above; 3. ability to comprehend Chinese; 4. fulfilling any 3 of the following criteria: i. morning stiffness  $\leq 30$  min; ii. crepitus on active joint motion; iii. bone tenderness; iv. bone enlargement; or v. no palpable joint warmth (This classification yielded 84% sensitivity and 89% specificity for OA knee diagnosis (14)); 5. having knee pain for at least 3 months (15); 6. Knee pain  $\geq 3$  on a Likert pain scale from 1–10; 7. having a smartphone (or a family member living together having a smartphone) that is compatible to WhatsApp (it is our experience in the pilot study that most of every subject had been used to using WhatsApp for social communication); and 8. willing to provide informed consent.

Exclusion criteria: 1. medical diagnoses or conditions that preclude individuals from active participation (e.g. bleeding disorders, alcohol or drug abuse); 2. knee pain related to other conditions (cancer, fracture, rheumatoid arthritis, rheumatism) as screened according to the red flags for further investigation or referral in the NICE 2014 Guidelines for Osteoarthritis of the knee (16); 3. score  $< 22$  in Hong Kong Montreal Cognitive Assessment (HK-MoCA) indicating cognitive impairment that may prevent understanding of training instructions (17); 4. body mass index over 30, the obese II criteria for Asians (18) (it will be too difficult for the obese subjects to perform acupressure on the acupoints as physical pressure reaching the muscle is required); 5. presence of skin lesions or infections at the treatment sites; 6. ever had knee replacement surgery; 7. pregnancy or contemplating pregnancy, and 8. ever received acupressure or steroid injection for knee pain over the past 6 months.

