**Table 1. Assessment Schedule**

|                                                                 | Screening | Baseline | Training period
(2 weeks) |   | Assessment
time points |   |    |
|-----------------------------------------------------------------|-----------|----------|------------------------------|---|---------------------------|---|----|
| Week of study                                                   | -1        | /        | 1                            | 2 | 4                         | 8 | 12 |
|                                                                 |           |          |                              |   |                           |   |    |
| Review inclusion/exclusion criteria                             | √         | √        |                              |   |                           |   |    |
| Demographics                                                    | √         |          |                              |   |                           |   |    |
| Medical History                                                 | √         |          |                              |   |                           |   |    |
| Height & Weight                                                 | √         |          |                              |   |                           |   |    |
| Vital signs                                                     | √         | √        | √                            | √ | √                         | √ | √  |
| Primary Outcome                                          |           |          |                              |   |                           |   |    |
| Pain Severity Numerical Rating Scale                            | √         | √        |                              |   | √                         | √ | √  |
| Secondary Outcomes                                       |           |          |                              |   |                           |   |    |
| Western Ontario and McMaster
University Osteoarthritis Index |           | √        |                              |   | √                         | √ | √  |
| Short Form-Six Dimensions                                       |           | √        |                              |   | √                         | √ | √  |
| Timed Up & Go Test                                              |           | √        |                              |   | √                         | √ | √  |

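### The 2-point NRS responder comparison uses an unadjusted chi-square: valid, but it gives up some power and cannot take the covariates the plan calls for

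*Protocol*

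**What the plan says.** Under Data management and analysis, the Protocol compares the primary and secondary outcomes with a linear mixed-effects model containing a group-by-time interaction. It then adds a responder analysis: "Clinical significance will be examined by the proportion of participants who have a reduction", defined as "a reduction of at least 2 points from baseline in the NRS using Chi-square test". That sentence names no covariate and no visit. Week 12 is taken here from the primary outcome in the Abstract.

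Two other sentences in the section bear on this. One sets a covariate rule: "any identified baseline difference was controlled as covariates". It is not limited to any one analysis. The other follows the responder sentence directly: "The intention-to-treat analysis will be conducted".

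Table 1 schedules the "Pain Severity Numerical Rating Scale" at baseline and at weeks 4, 8 and 12, so the adjusting variable is already collected. The Sample size calculation concerns the difference in mean NRS. No power is stated for the responder proportion.

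**The concern.** Response is a fall of a fixed number of points, so people who start low have less room to respond than people who start high. Baseline NRS enters the definition of response, but that does not remove its influence on who responds. It leaves a strong prognostic factor unused in the comparison between arms.

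Two things follow. Some power is given up on the one analysis meant to show whether the effect matters to patients. And if the arms differ in baseline NRS by chance, the section tells the analyst to control for the difference, while the test it names for this endpoint takes no covariates.

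**Working it through.** **1. The plan's own figure.** For a difference in means with effect size 0.40, two-sided alpha 0.05 and 90% power: n per arm = 2 × (1.960 + 1.282)² / 0.40² = 131.3, so 132. The t-based calculation gives 132.3, so 133 as stated. With 15% attrition, 133 / 0.85 = 156.5, so 157 per arm and 314 in total. The stated size reproduces, and it covers the comparison of means only.

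**2. Inputs for the responder analysis.**
- From the Protocol: 133 per arm, effect size 0.40, pilot SDs 1.47 and 1.58. Pooled SD = √((1.47² + 1.58²)/2) = 1.53, so the mean difference is 0.40 × 1.525 = 0.61.
- Assumed, because the Protocol does not give them: baseline NRS normal with mean 5 and SD 1.5, rounded and kept within 3 to 10; week-12 SD 1.5; control-arm mean fall 1.3; baseline-to-week-12 correlation r from 0.2 to 0.6.

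**3. How far response depends on baseline.** For a participant starting at b, the control-arm week-12 mean is 3.7 + r(b − 5) and the SD is 1.5√(1 − r²). With whole-number scores, response means an underlying week-12 value below b − 1.5. At r = 0.4 the SD is 1.375:
- b = 4, control: Φ((2.5 − 3.3)/1.375) = 0.28; acupressure (mean 0.61 lower): Φ((2.5 − 2.69)/1.375) = 0.44.
- b = 7, control: Φ((5.5 − 4.5)/1.375) = 0.77; acupressure: Φ((5.5 − 3.89)/1.375) = 0.88.

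Within either arm, the spread between these two starting scores is much larger than the difference between arms.

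**4. Power at 133 per arm** (1,500 simulated trials per row; Pearson chi-square against logistic regression with baseline NRS):

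| Correlation | Chi-square | Adjusted logistic | Gain (points) |
|---|---|---|---|
| 0.2 | 0.571 | 0.675 | 10 |
| 0.4 | 0.686 | 0.756 | 7 |
| 0.5 | 0.776 | 0.819 | 4 |
| 0.6 | 0.871 | 0.903 | 3 |

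A separate simulation gave 0.57 against 0.67 (r = 0.2), 0.62 against 0.68 (0.3), 0.73 against 0.78 (0.5) and 0.86 against 0.89 (0.6), so gains of 10, 6, 5 and 3 points.

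**5. What adjustment does not recover.** In the same simulated trials, a baseline-adjusted comparison of mean NRS had power 0.91, 0.94, 0.96 and 0.98. Most of the shortfall comes from cutting the score into response and non-response. A closed-form check agrees. Take the pilot's fall of 2.27 (SD 1.2) for acupressure and 2.27 − 0.48 = 1.79 for control. The response rates are Φ(0.27/1.2) = 0.589 and Φ(−0.21/1.2) = 0.431, with chi-square power about 0.74 at 133 per arm. Other mean falls, with SDs of 1.2 to 1.53, give 0.67 to 0.74.

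**6. Type I error.** With no treatment effect (r = 0.4) the chi-square rejected in 4.8% of 1,500 trials. Exact enumeration at 133 per arm and a common response rate of 46% gives 5.6%. The test is sound overall.

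**7. The covariate rule.** A 2×2 chi-square compares two proportions and has no place for a covariate. The rule would matter when the arms differ by chance. In simulated null trials where mean baseline NRS differed by more than 0.25 points (about 13 to 14% of trials), the chi-square rejected 10 to 11% of the time, against 4 to 6% for the adjusted model.

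**The case against.** The strongest reply is that this is a preference about a supportive analysis. Randomisation balances baseline NRS in expectation, the chi-square holds its error rate, the main inference rests on the mixed model, and no power is promised for responders. The gain is modest and depends on inputs the Protocol does not give. Most of the loss comes from dichotomising, which adjustment leaves in place. The covariate rule might also have been meant for the mixed model only. All of this stands as to priority. It does not remove the point: the Protocol names the test, a better one uses data already collected, and the covariate sentence carries no restriction to the mixed model.

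Three stronger readings are tempting, and the documents do not support them.
- A reader might infer that the chi-square can only use participants with an observed week-12 score. Nothing says so. Missing responses can be imputed or counted as non-response in a 2×2 table, and that rule may sit in an SAP that is not shown.
- A reader might infer a conflict with the intention-to-treat statement. The Protocol states the principle and states no exclusion, so there is no contradiction.
- A reader might link the floor on response to the entry criterion, which is set "on a Likert pain scale from 1–10" while the outcome NRS runs from 0 to 10 and is also listed at screening. That mismatch is real and the passages should be reconciled. It is a separate eligibility point, and it does not show the test to be wrong.

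**Conclusion.** The point holds as one of efficiency and internal consistency, at minor priority. The unadjusted chi-square is valid but gives up about 3 to 10 power points at 133 per arm and effect size 0.40. It also cannot apply the section's covariate rule to this endpoint. The size rests on the assumed baseline distribution and on correlations of 0.2 to 0.6: the gain is largest when baseline and week-12 scores are weakly correlated and smallest when they are strongly correlated. The documents do not support a claim of bias, of a completers-only analysis or of a breach of intention-to-treat.

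**What to change.** Replace the chi-square with a logistic regression of week-12 response (a fall of 2 or more NRS points) on arm, with baseline NRS as a prespecified covariate whether or not the arms are seen to differ, in all randomised participants. Report the adjusted risk difference, obtained by averaging the fitted response probabilities under each arm, with its confidence interval. Name week 12 in the sentence. The same model can take any further covariate that the section's rule calls for.

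The cost is a change of wording and slightly more analysis work, mainly the step from the logistic fit to a risk difference. No new data are needed and the sample size is unaffected.
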